## Abstract

**Background:**

Cervical cerclage is a recognised treatment to prevent late miscarriage and pre-term birth (PTB). Emergency cervical cerclage (ECC) for cervical dilatation with exposed unruptured membranes is less common and the potential benefits of cerclage are less certain. A randomised control trial is needed to accurately assess the effectiveness of ECC in preventing pregnancy loss compared to an expectant approach.

**Methods:**

C-STICH2 is a multicentre randomised controlled trial in which women presenting with cervical dilatation and unruptured exposed membranes at 16 + 0 to 27 + 6 weeks gestation are randomised to ECC or expectant management. Trial design includes 18 month internal pilot with embedded qualitative process evaluation, minimal data set and a within-trial health economic analysis.

Inclusion criteria are ≥16 years, singleton pregnancy, exposed membranes at the external os, gestation 16 + 0–27 + 6 weeks, and informed consent. Exclusion criteria are contraindication to cerclage, cerclage in situ or previous cerclage in this pregnancy.

Randomisation occurs via an online service in a 1:1 ratio, using a minimisation algorithm to reduce chance imbalances in key prognostic variables (site, gestation and dilatation). Primary outcome is pregnancy loss; a composite including miscarriage, termination of pregnancy and perinatal mortality defined as stillbirth and neonatal death in the first week of life. Secondary outcomes include all core outcomes for PTB. Two-year development outcomes will be assessed using general health and Parent Report of Children’s Abilities-Revised (PARCA-R) questionnaires. Intended sample size is 260 participants (130 each arm) based on 60% rate of pregnancy loss in the expectant management arm and 40% in the ECC arm, with 90% power and alpha 0.05. Analysis will be by intention-to-treat.

**Discussion:**

To date there has been one small trial of ECC in 23 participants which included twin and singleton pregnancies. This small trial along with the largest observational study (*n* = 161) found ECC to prolong pregnancy duration and reduce deliveries before 34 weeks gestation. It is important to generate high quality evidence on the effectiveness of ECC in preventing pregnancy loss, and improve understanding of the prevalence of the condition and frequency of complications associated with ECC. An adequately powered RCT will provide the highest quality evidence regarding optimum care for these women and their babies.

**Trial registration:**

ISRCTN Registry ISRCTN12981869. Registered on 13th June 2018.

## Background

Prevention of second trimester miscarriage and preterm birth (PTB) are important public health priorities. Stillbirth and delivery before 37 completed weeks of gestation are major contributors to pregnancy loss and the prevalence of significant morbidities among survivors following PTB at low gestational ages remains of concern, despite improving survival (BAPM Framework ADC 2019). These two conditions frequently share common aetiologies, namely cervical insufficiency and infection [14] and the management of women at risk of miscarriage or PTB remains broadly similar. Cervical cerclage by placing a stitch around the cervix has been shown to be effective at reducing the risk of second trimester miscarriage or PTB in women with a closed cervix and cervical insufficiency identified by clinical history or ultrasound findings [13]. Planned cerclage or cerclage in response to a shortened cervix is associated with an increased proportion of deliveries above 35 weeks [2].

Less frequently, in the second trimester a woman may present with a cervix that is already dilated exposing the foetal membranes. In this situation an emergency cervical cerclage (ECC) or ‘rescue’ stitch can be attempted, with the intention of prolonging the pregnancy, preventing miscarriage or very early PTB, with the goal of improved neonatal outcomes [1]. The risks of this procedure are poorly described and are likely to be higher than in a planned procedure with a closed cervix [19]. These include a risk of membrane rupture during the procedure, leading to pregnancy loss or delivery at an earlier gestation than would have occurred without intervention [6]. In addition, there is risk of infection and potential harm to the mother or her baby, a risk of damage to the cervix and a risk of bleeding [10].

Few studies have investigated ECC. The majority have used an observational design [10], with one randomised controlled trial (RCT). This RCT included only 23 women, 13 allocated to ECC plus indomethacin and 10 to bed-rest [1]. The trial could not separate out the effect of indomethacin as a tocolytic from cerclage. Furthermore, over one third of the participants in this trial had twin pregnancies; in contrast to singleton pregnancies, there is no evidence to support the use of cerclage in multiple pregnancy [15]. Despite the small trial size and these limitations, the mean time to delivery was longer in the ECC arm (54 vs 20 days, *p* = 0.05) and the proportion who delivered before 34 weeks was reduced (54% vs 100%, *p* = 0.02) [1].

The evidence for ECC was reviewed by NICE [11], which concluded that there may be benefit from ECC but that further evidence was required. In response to this we have designed C-STICH2 (Emergency Cervical Cerclage to Prevent Miscarriage and Preterm Birth), an open, multicentre randomised controlled trial to determine whether ECC improves maternal and infant outcomes in women who present with cervical dilatation and exposed unruptured foetal membranes, compared to routine expectant management. This protocol describes an internal pilot to determine feasibility and the procedure for a full RCT.

## Methods/design

### Aims and objectives

The aims and objectives of the C-STICH2 trial are presented in Table 1.

**Table 1 Tab1:** Description of the aims and objectives of C-STICH2 internal pilot and full trial

Aim: To evaluate whether ECC can improve outcomes for mothers and babies’ in women who present with cervical dilatation and exposed unruptured foetal membranes.	
**Pilot objectives**	• To ascertain if the trial and trial processes are acceptable to women, including the ability to recruit and randomise women. • To assess whether the event rate of the primary outcome is compatible with the estimate used in the sample size calculation. • To explore if clinicians are in equipoise and willing to randomise to an RCT.
**Full trial objectives**	• To determine whether an ECC reduces pregnancy loss (miscarriage, termination of pregnancy, stillbirth or neonatal death within 7 days of delivery) in women who present with cervical dilatation and exposed, unruptured foetal membranes between 16 + 0 and 27 + 6 weeks. • To follow up all surviving babies to 2 years of corrected age to determine their general health and medium-term neurodevelopmental outcomes. • To determine the complication rates of ECC: iatrogenic rupture of membranes during the procedure; insertion failure; predictors of successful ECC placement such as magnitude of dilatation

### Study design and setting

C-STICH2 is an open, multicentre, superiority, RCT in the UK. There is an internal pilot with an embedded qualitative process evaluation. The full trial includes a within-trial economic analysis and a minimal dataset of anonymised demographic and pregnancy outcome data from all women presenting with the condition who do not consent to participate in the randomised arms of C-STICH2.

### Participants

Women will be considered eligible for C-STICH2 if they are aged 16 years or over, with a singleton pregnancy and in whom the cervix is found to be dilated with the foetal membranes intact and exposed, at or below the level of the external os, based on judgement. This may be diagnosed on speculum examination or by ultrasound finding, if performed by a suitably trained practitioner. The gestational age of the pregnancy must be 16 + 0 to 27 + 6 weeks based on the best available estimate and the woman must be able to provide written informed consent. The exclusion criteria are as follows: contra-indication to ECC as judged by the responsible clinician; if the participant has already received cervical cerclage of any type in this pregnancy, or has a cerclage in situ from a previous pregnancy.

### Participant enrolment

Participants will be identified following clinical presentation to maternity assessment units, or women may be identified through screening in a specialist PTB clinic setting (Fig. 1). Women who meet the eligibility criteria should be approached by the most senior clinician available about participating in the trial. It is recognised that this may be a very difficult time for women and their families and sufficient time will be given for women to consider participation and explore options. The clinician should be familiar with counselling women at risk of preterm delivery and have received training from the trial team or principal investigator. A detailed participant information sheet (PIS) will be provided. If the woman agrees to participate, written consent must be obtained prior to randomisation. Participants must understand that they are free to withdraw from the trial at any time and that this will not affect their subsequent care.

**Fig. 1 Fig1:**
[figure not shown]
C-STICH2 flow diagram

In women who decline to participate in the randomised arms of C-STICH2 or who are not approached regarding the study, a non-consented anonymised minimal dataset will be collected. This dataset includes basic demographics and pregnancy outcome data to inform overall prevalence of the condition and incidence of pregnancy loss.

### Qualitative process evaluation

All women approached about the trial should be informed about the qualitative process evaluation, even if they have chosen to decline trial participation. They will receive written information about participation in the qualitative study either at the time of presentation and trial approach, shortly after at a time considered appropriate by their healthcare professionals (HCPs), at a follow-up appointment, or via a follow-up letter. Women who express an interest in participating will, where feasible, be asked to complete and sign a consent to contact form giving written permission to be contacted by the qualitative research team. Women who are sent a follow-up letter about the qualitative study will be asked to return a completed consent to contact form or will be able to contact the research team directly. Following receipt of the consent to contact form or direct contact, the qualitative team will assess suitability of contact timing with the recruiting site. If this is deemed to be appropriate, the team will then discuss participation with the woman and separate informed consent (written, electronically completed or verbal) for the qualitative study will be obtained. The qualitative process evaluation will use semi-structured interviews to explore women’s experiences of diagnosis and care, and their views of the trial processes irrespective of their decision to participate in C-STICH2.

HCPs named on the site delegation logs will also be approached directly by the qualitative research team to participate in semi-structured interviews to help inform our understanding of the following: issues approaching women to participate, views on barriers and facilitators to trial recruitment, thoughts and experiences on the use of ECC including personal and community equipoise. All participants will complete a demographic questionnaire to inform sampling and subsequent description of participant characteristics.

Women and HCPs will be able to choose how they participate in an interview (e.g. face to face, via phone, or via video calling). Interviews will be digitally-audio recorded with data collection and initial analysis taking place iteratively [3]. We anticipate undertaking up to 50 interviews in total but the numbers will remain flexible to ensure that we collect sufficiently rich data to address the aims and objectives of the study [8]. Audio files will be transcribed clean verbatim by a specialist transcription company and the framework approach [4] used to facilitate a systematic and flexible approach to the analysis.

The findings from the qualitative process evaluation will dynamically inform trial design both during and subsequent to the pilot [12]. The embedded qualitative findings will influence trial processes moving beyond the pilot study, inform trial steering committee (TSC) recommendations and help to maximise recruitment and retention in this challenging setting.

### Randomisation and blinding

After eligibility has been confirmed and informed consent obtained, women can be randomised into the C-STICH2 trial (Fig. 1). Randomisation will be provided by a secure 24/7 online randomisation system and a backup free telephone randomisation service (available during working hours). Randomisation can be completed by any staff member on the delegation log assigned to do so. Participants will be randomised in a 1:1 ratio to either ECC or expectant management. A minimisation algorithm will be used to ensure balance in the treatment allocation by site, gestation (16 + 0–19+ 6/20+ 0–23+ 6/24+ 0–27+ 6 weeks) and cervical dilatation (≤3 cm ≥ 4 cm/fully dilated-minimal cervix felt). A ‘random element’ will be included in the algorithm, so that each participant has a probability (unspecified here) of being randomised to the opposite treatment that they would have otherwise received.

It is not possible to blind women or clinicians to the intervention they have received as the comparison is between a surgical intervention and expectant management. The primary outcome (miscarriage, stillbirth, termination of pregnancy and neonatal death) is, however, objective and thus should minimise bias.

### Trial interventions

This trial will be pragmatic in nature allowing the use of treatment adjuncts such as antibiotics or indomethacin in both the ECC and expectant management arms following randomisation.

For women allocated to ECC, this should be delivered at a time that is felt to be clinically appropriate and within 72 h of randomisation. An ECC will involve, under appropriate anaesthesia, the replacement of the foetal membranes into the uterine cavity and the placement of a “purse string” cervical cerclage around the body of the cervix, aiming to occlude the cervical canal and prevent further prolapse of the foetal membranes. Pre-operative, operative, and post-operative management is at the discretion of the clinician responsible for the woman.

Women allocated to expectant management will be managed pragmatically according to local protocols. If an ECC is placed, this will be considered a protocol deviation.

### Follow-up

Surviving children will be followed up at 2 years of corrected age. On discharge from hospital, consent for long-term follow-up will be confirmed and contact details for the main carer will be collected. The research team will maintain contact with families of surviving children at intervals to minimise loss to follow-up. At 2 years corrected age, the main caregiver will be sent questionnaires, this will include general health, Parent Report of Children’s Abilities-Revised (PARCA-R) questionnaire [7, 9] and an assessment of motor outcomes.

### Adverse event reporting

Adverse outcomes, both maternal and neonatal, are common in this high-risk obstetric population. Adverse events (AEs) will be reported via case report forms (CRF) and captured via pre-defined outcome measures. Serious adverse events (SAEs) including but not limited to maternal admission requiring care in high dependency units (HDU) or intensive treatment units (ITU), life-threatening maternal conditions and maternal complications associated with ECC will be reported directly to the trial office and may require expedited reporting. It is recognised that some SAEs are to be expected in these women either as an outcome or known risk of the intervention and whilst it is important that they are reported, this can be done within the relevant CRF. Examples include but are not limited to miscarriage, preterm delivery, admission to hospital for delivery or removal of suture, damage to cervix during ECC insertion or admission to a neonatal unit.

### Outcome measures

The primary outcome is pregnancy loss defined as miscarriage, termination of pregnancy and perinatal mortality defined as stillbirth and neonatal death in the first week after birth. Secondary outcomes are detailed in Table 2. All the core outcomes for PTB are included [17].

**Table 2 Tab2:** Full description of all secondary outcomes including complete core outcome set for preterm birth

**Secondary outcomes—maternal, neonatal and paediatric**	
**Maternal**	
Pregnancy loss (miscarriage, termination of pregnancy and perinatal mortality, including any stillbirth or neonatal death in the first week of life). Excluding those due to congenital anomalies (chromosomal and/or structural) assessed via death certification.	
Time from conception to pregnancy end (any reason)	
Miscarriage and pre-viable neonatal death (defined as delivery < 24 weeks)	
Stillbirth (defined as intrauterine death ≥ 24 weeks)	
Gestation at delivery	
Pre-term delivery (pre-specified groups of ≤ 28/≤ 32/≤ 37 weeks)	
Maternal sepsis (at any time in pregnancy and until discharge from hospital postnatally)	
Preterm (< 37 weeks) pre labour rupture of membranes (> 24 h prior to delivery) (PPROM) adjusting for gestational age at occurrence of membrane rupture	
Mode of initiation of birth (spontaneous or iatrogenic)	
Indication for iatrogenic delivery (maternal and/or foetal)	
Mode of delivery (vaginal or operative vaginal or caesarean)	
Cerclage placement complications assessed as a composite and individually: cervical laceration; bleeding from cervix; ruptured membranes; bladder injury	
Cerclage removal complications assessed as a composite and individually: cervical tears; difficulty in removal defined as requiring unexpected anaesthesia or unexpected dissection of suture	
Suspected or confirmed chorioamnionitis (during pregnancy and up to 7 days postnatally)	
Maternal admission to HDU or ITU pre-delivery	
Maternal admission to HDU or ITU post-delivery	
Serious adverse events	

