**Neonatal**	
Early neonatal death (defined as a death within 7 days after delivery)	
Late neonatal death (defined as a death beyond 7 days and before 28 days after delivery)	
Early neonatal death (defined as a death within 7 days after delivery excluding those secondary to congenital anomalies)	
Late neonatal death (defined as a death beyond 7 days and before 28 days after delivery excluding those secondary to congenital anomalies)	
Birth weight adjusted for gestational age and sex	
Small for gestational age (< 10th centile)	
Advanced resuscitation at birth (assisted ventilation and/or drug administration and/or cardiac compressions)	
Admission to specialist care (SCBU/NICU/HDU/transitional care)	
Length of stay in each additional specialist care setting	
Suspected sepsis (clinically diagnosed defined as commenced on intravenous antibiotics for > 48 h after birth)	
Confirmed sepsis (positive microbiology)	
Brain injury (defined as any intraventricular haemorrhage (IVH) (excludes subependymal haemorrhages), parenchymal cystic or haemorrhagic lesion or persistent ventriculomegaly (VI > 97th percentile)	
Respiratory support (ventilation/CPAP)	
Days on respiratory support	
Supplementary oxygen requirements at 36 weeks corrected gestational age	
Necrotising enterocolitis (Bell’s stage 2 or 3)	
Retinopathy of prematurity requiring laser treatment	
Disabilities	
Congenital abnormalities	
Serious adverse events	

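### The anomaly-excluded pregnancy-loss outcome names death certification as its only source, so if early losses are generally uncertified it cannot remove anomaly-related miscarriages and terminations before 24 weeks

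*Protocol article*

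**What the plan says.** The Outcome measures section of the protocol article defines the primary outcome without regard to cause: "The primary outcome is pregnancy loss defined as miscarriage, termination of pregnancy and perinatal mortality defined as stillbirth and neonatal death in the first week". The maternal rows of Table 2 then repeat that composite as a secondary outcome, "Pregnancy loss (miscarriage, termination of pregnancy and perinatal mortality, including any stillbirth or neonatal death in the first week of life", and qualify it: "Excluding those due to congenital anomalies (chromosomal and/or structural) assessed via death certification". This is the only source named, and it covers all components of the composite.

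The same table separates early from late losses: "Miscarriage and pre-viable neonatal death (defined as delivery < 24 weeks" in one row and "Stillbirth (defined as intrauterine death ≥ 24 weeks" in another. On entry, the Participants section says: "The gestational age of the pregnancy must be 16 + 0 to 27 + 6 weeks based on the best available estimate". Under Randomisation and blinding, two of the three gestation bands used for minimisation lie wholly below 24 weeks, and neither women nor clinicians are blinded.

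Two neonatal entries in Table 2 also bear on this. One lists "Congenital abnormalities" as an outcome, without linking it to the pregnancy-loss exclusion. The other is "Early neonatal death (defined as a death within 7 days after delivery excluding those secondary to congenital anomalies", with a matching row for late neonatal death; neither death row names a source.

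**The concern.** Excluding losses by cause works only if the chosen source can give a cause for each kind of loss in the composite. Here one source has to serve miscarriage, termination, stillbirth and first-week neonatal death. With entry from 16+0 weeks, losses before 24 weeks are a planned part of the outcome. If those losses generally carry no certificate stating a cause, the rule has nothing to read for them, and an anomaly-related miscarriage or termination is counted as though it were not anomaly-related.

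At stake is whether the outcome measures what its label says. A termination for fetal anomaly is the plainest example of a loss the label promises to leave out, and it may be one that this rule cannot identify. A report could then suggest that anomaly-related losses had been set aside when some had not been detectable.

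**Working it through.** **Step 1. The plan's own figure.** Inputs from Sample size estimates: 60% against 40%, 90% power, α = 0.05 (two-sided assumed), equal arms. With pooled variance and no continuity correction,

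n per arm = [1.960 × √(2 × 0.5 × 0.5) + 1.282 × √(0.6 × 0.4 + 0.4 × 0.6)]² / 0.2² = (1.386 + 0.888)² / 0.04 ≈ 129.3, rounded up to 130.

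That gives 260 in total, as stated, with power 0.902. Expected losses are 0.6 × 130 + 0.4 × 130 = 78 + 52 = 130. None of this depends on the anomaly exclusion.

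**Step 2. The rule set against each component.** The last column rests on the certification assumption, which is not in the documents.

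| Component | Gestation in the article | Can certification give a cause? |
|---|---|---|
| Miscarriage | below 24 weeks | no, if generally uncertified |
| Termination | no limit stated | no before 24 weeks, if generally uncertified; yes later, if certified |
| Stillbirth | 24 weeks or later | yes, taken as certified |
| First-week neonatal death | any, including pre-viable live births | yes, taken as certified |

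**Step 3. Effect on the relative risk.** The documents give no rate of anomaly-related loss, so a range is used. Let *a* be the proportion of women in each arm with an uncertified anomaly-related loss, equal in both arms and unaffected by cerclage. Let the total loss rate under expectant management be 0.6 and the true relative risk for all other losses be 2/3. If the *a* losses stay in,

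observed RR = [(2/3)(0.6 − *a*) + *a*] / 0.6 = 2/3 + *a*/1.8.

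| *a* | Losses left in per arm (130 × *a*) | Observed RR | Power, losses removed | Power, losses left in |
|---|---|---|---|---|
| 0 | 0 | 0.667 | 0.902 | 0.902 |
| 1% | 1.3 | 0.672 | 0.892 | 0.892 |
| 2% | 2.6 | 0.678 | 0.881 | 0.881 |
| 3% | 3.9 | 0.683 | 0.870 | 0.870 |
| 5% | 6.5 | 0.694 | 0.847 | 0.845 |

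The shift is towards no effect, and the two power columns differ by less than half a percentage point.

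**Step 4. The same range as a share of losses.** If 2% to 5% of the 130 expected losses were anomaly-related (assumed), that is 2.6 to 6.5 losses in the whole trial. If 50% to 100% of these were uncertified (assumed), 1.3 to 6.5 would stay in, or 0.5% to 2.5% of 260 women. The formula then gives an RR of 0.669 to 0.681. The 5% row in Step 3 is 13 of 260 women, about 10% of the planned losses, so it serves as an upper case.

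**The case against.** The strongest objection is that the deciding premise lies outside the documents. Nothing in the article says which losses receive a certificate, and its 24-week boundary defines miscarriage and stillbirth without mentioning certification. That stands. The premise is therefore stated as an assumption, and the range includes zero.

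A reader might go further and infer that all anomaly-related miscarriages and terminations remain in the outcome. The documents do not support that. Later terminations could be certified, as could deaths after a pre-viable live birth, and no gestational distribution of losses is given.

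A reader might also expect that a result close to the primary outcome would show the rule had failed. It would not. If anomaly-related losses are few, the two results will be close whatever source is used. Nor does the article say that this outcome was meant as a check on the primary result.

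The article is condensed, and a fuller protocol or the SAP may set out sources by component. But Table 2 is captioned as a full description and does name a source. The point is about a rule that is stated, not about detail left elsewhere.

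Two objections concern the remedy, and both have force. First, a certificate is a formal record made outside the trial, whereas clinical diagnoses in an open trial bring uneven investigation and attribution by people who know the allocation. Second, the article does not show that the needed data exist: congenital abnormalities appear only among the neonatal outcomes, and no field for the reason for termination, genetic result or post-mortem is shown. The remedy has to allow for both.

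**Conclusion.** The point holds as a minor one. The article fixes a single source for a composite in which that source may not reach miscarriages and terminations before 24 weeks. If those losses are generally uncertified, the rule cannot remove the anomaly-related ones among them.

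The size is small. The relative risk would read about 0.67 to 0.69 instead of 0.667 if 1% to 5% of women per arm were affected. This rests on equal anomaly-related rates in both arms and no effect of cerclage on them. There is no effect at all if every loss is certified.

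A reader might infer that the primary result or the sample size is in doubt. Neither is, because the primary outcome has no anomaly exclusion. A reader might also infer that the anomaly-excluded early and late neonatal death rows share the fault. No problem is shown there, since certification suits those deaths best.

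**What to change.** In the Table 2 row, and in the SAP to match, replace the closing words on how anomaly is assessed with: *assessed via death certification where a certificate exists and, for other losses, from the recorded antenatal, post-mortem or genetic diagnosis of anomaly or the recorded reason for termination, with attribution made blind to allocation*. State also that early losses without any investigation are counted as not anomaly-related. Leave the neonatal death rows as they are.

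The cost is some extra data checking for early losses and possibly one added case report form item. Two limits remain. Uninvestigated early losses cannot be classified under any rule. Blind attribution guards against biased judgement but not against differences in how often clinicians investigate.

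### The secondary outcome PPROM is adjusted for gestational age at membrane rupture, a post-randomisation variable that forms part of the outcome's own definition

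*Protocol article*

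**What the plan says.** The Maternal block of Table 2 (Outcome measures) defines the event as "Preterm (< 37 weeks) pre labour rupture of membranes (> 24 h prior to delivery", and the same row fixes the covariate: "PPROM) adjusting for gestational age at occurrence of membrane rupture".

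Three other places bear on it.

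- **Participants.** Eligible women are those "in whom the cervix is found to be dilated with the foetal membranes intact and exposed".
- **Background.** ECC is attempted "with the intention of prolonging the pregnancy, preventing miscarriage or very early PTB". Of its risks the article says: "These include a risk of membrane rupture during the procedure, leading to pregnancy loss or delivery at an earlier gestation".
- **Statistical analysis.** Binary secondary outcomes follow the primary: a log-binomial model giving a relative risk, adjusted for the minimisation variables, by intention to treat. Under Randomisation and blinding those variables are site, gestation band and cervical dilatation, all known at randomisation.

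No section explains why PPROM is treated differently.

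**The concern.** An adjusted comparison keeps the protection of randomisation only if the covariates are fixed before allocation. Gestation at rupture is not. Every participant's membranes are unruptured at entry, so the value comes later, and by the article's own account ECC may delay rupture or cause it. The covariate also helps decide the outcome, because a woman whose membranes rupture at 37 weeks or later cannot be a case.

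This matters because PPROM is the only row in Table 2 that compares membrane rupture between the two arms. The other rupture item, under cerclage placement complications, can occur only where a cerclage is attempted. If the PPROM relative risk is not interpretable, the trial has no planned randomised comparison of an event that the procedure may either prevent or provoke.

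**Working it through.** **The article's checkable figure.** It gives no number for PPROM. Its sample size reproduces. With 60% v 40%, two-sided 0.05 (assumed two-sided), 90% power and a pooled average of 0.5, n per arm = [1.960 × √(2 × 0.5 × 0.5) + 1.282 × √(0.6 × 0.4 + 0.4 × 0.6)]² / 0.2² = (1.386 + 0.888)² / 0.04 ≈ 129.3. That rounds up to 130, or 260 in total. Nothing below touches it.

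**What the adjusted model can be.** The row does not say for whom gestation at rupture is recorded, so there are two cases.

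1. *Recorded only for women with PPROM.* Every woman with a covariate value has the event. The outcome does not vary, so no relative risk can be estimated.
2. *Recorded for every rupture.* Split the risk as P(PPROM) = P(rupture < 37 weeks) × P(pre-labour, > 24 h, given rupture < 37 weeks). The effect in all randomised women is the product of a timing ratio and a pre-labour ratio. Holding gestation at rupture fixed takes out the timing ratio, which is the part ECC is meant to act on. What is left compares women who ruptured at the same gestation, and randomisation did not make those women comparable.

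**Illustration of case 2.** There were 200,000 simulated women per scenario, fitted with a log-link Poisson model.

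- From the document: "the mean time to delivery was longer in the ECC arm (54 vs 20 days" in the one earlier small trial, that is 54/7 = 7.7 and 20/7 = 2.9 weeks. These are times to delivery, borrowed here as mean times from randomisation to rupture.
- Assumed: exponential intervals, gestation at entry uniform over 16 to 28 weeks, and the pre-labour shares shown.
- Base model: arm and gestation at randomisation. Adjusted models: these plus gestation at rupture, either as a linear term or in bands among ruptures before 37 weeks.

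| Scenario | PPROM, expectant v ECC | RR, base | RR, + rupture gestation (linear) | RR, within bands < 37 weeks |
|---|---|---|---|---|
| (a) ECC only delays rupture; pre-labour share 40% in both arms | 39.5% v 33.6% | 0.85 | 1.02 | 1.00 |
| (b) As (a), plus an unmeasured common cause of early and of pre-labour rupture | 40.2% v 35.5% | 0.88 | 1.16 | 1.13 |
| (c) Delay, and pre-labour share 50% v 40% | 49.2% v 33.5% | 0.68 | 0.82 | 0.80 |

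**Check by hand.**

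- In (a), P(rupture < 37) is 39.5/40 = 0.99 v 33.6/40 = 0.84, a timing ratio of 0.85. The pre-labour ratio is 40/40 = 1.00. The total is 0.85, and 1.00 remains once timing is held fixed.
- In (c), the pre-labour ratio is 40/50 = 0.80. The total is 0.85 × 0.80 = 0.68, and 0.80 remains.
- In (b), the figure passes 1 because ECC women who rupture as early as controls are, on average, at higher underlying risk. Conditioning on rupture time brings that selection into the comparison.

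**The case against.** **The SAP may sort this out.** The article is a summary, and its general rule points to baseline covariates. But the row itself specifies the adjustment, in a table titled as a full description of the secondary outcomes. A statistician following the row would fit the wrong model.

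**The intention may have been sensible.** Rupture at 20 weeks and rupture at 36 weeks are different events, and the authors may have meant only that timing be shown. If so, the word for adjusting is the wrong one and the same edit is needed. What stands is that gestation at rupture is worth reporting.

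**The simulated sizes are partly built in.** This is right. Scenario (a) assumes that ECC acts only through timing, so holding timing fixed must give about 1. The figures show a mechanism and do not forecast this trial. A reader might infer that the adjustment must erase or reverse the effect. The documents do not support that: scenario (c) shows attenuation only, and the article does not say how ECC acts on pre-labour rupture.

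**Procedural rupture is captured elsewhere.** It is, as a placement complication and as a trial objective, without this covariate. That covers part of the safety question, but it gives no comparison between arms.

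**Birth weight.** A reader might also infer that "Birth weight adjusted for gestational age and sex" has the same fault, since gestation at birth is post-randomisation too. The documents do not support calling it an error. The row sits directly above "Small for gestational age (< 10th centile" and reads as the continuous size-for-gestation measure beside it. Nothing presents it as ECC's total effect on weight. Gestation at delivery, time to pregnancy end and preterm delivery are listed without such adjustment, so the effect on duration is measured. A row in raw grams would be an added outcome, and it too would be conditional on having a recorded weight. All that is needed is not to read the adjusted figure as the total effect of ECC on birth weight.

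**Conclusion.** The PPROM row is wrong as written. That conclusion needs no simulation. It follows from the intact membranes at entry, the stated purpose and risk of ECC, and the 37-week limit in the definition. Depending on how rupture timing is recorded, the relative risk either cannot be estimated or is not the intention-to-treat effect that the article promises.

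The size of the distortion is not known. On assumed inputs, a protective relative risk moved from 0.85 to about 1.0, from 0.68 to about 0.82, or from 0.88 to about 1.15. It can therefore be removed, attenuated or reversed, according to mechanisms the article does not state.

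The consequence is limited to one secondary outcome. The primary analysis and the sample size of 260 stand. It should be corrected before the analysis but does not threaten the trial's main conclusion.

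**What to change.** In Table 2, end the PPROM row at its definition and delete the clause on gestational age at rupture. Analyse PPROM in all randomised women by the model already planned for binary secondary outcomes, adjusted only for site, gestation at randomisation and cervical dilatation. Report gestation at rupture descriptively by arm. Make the same change in the SAP if it repeats the clause.

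No row needs to change for birth weight. When reporting, describe the gestation- and sex-adjusted figure as a growth measure.

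The cost is one wording change, with no new data and no effect on sample size. It should be made before anyone sees outcome data by arm, because dropping a covariate afterwards would look data-driven.
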